### **4.2 Organisation of data and analyses**

Data are collected at 5-7 assessment points, depending on the outcome measure. Data points include baseline, 3 weeks into treatment (3WK), 5 weeks into treatment (5WK), directly after the 10-week treatment (post-treatment), and 3, 6, and 12 months post-treatment (3FU, 6FU, and 12FU, respectively). Analyses will be performed in two stages. Stage 1 corresponds to paper 1 (see section 3. Reporting), and will contain data collected between baseline and the 3FU (the primary endpoint). Stage 2 corresponds to paper 2 (see section 3. Reporting), and will contain data collected at all assessment points, from baseline up to the 12FU. The two-stage analysis will require two corresponding database locks. The primary outcome analysis will be carried out in stage 1 (corresponding to objective #1).

The primary data analysis will be conducted after the last participant has completed the 3FU and all collected data have been entered into the trial database. Assessors will however remain blind for the individual participants' treatment allocations until data for the final 12FU assessment has been conducted. The SAP will be finalised, approved, and published prior to unblinding.

### **4.3 *Interim analyses***

No interim analyses are planned.

### **4.4 *Recruitment and retention***

A CONSORT 2010 flow diagram [3] will be presented to provide a detailed description of the participant flow throughout the study, including number of participants screened, reasons for exclusion, number of participants randomised to each group, and number of participants assessed at each follow-up point. See CONSORT flow diagram [3] for the exact content that will be presented.

### **4.5 *Description of demographic variables at baseline***

The demographic information collected at baseline will be summarised and presented in a table, by randomisation arm. Categorical variables will be reported as counts and percentages. Continuous variables will be summarised as means, medians, and interquartile ranges, as appropriate. According to CONSORT recommendations, no statistical tests will be performed to assess baseline differences between study arms [5].

### **4.6 *Protocol deviations***

Protocol deviations which could impact on the results of the analyses (such as concomitant psychological treatment or medication) will be described in detail. Further analyses taking such deviations into account (e.g., sensitivity analyses) may be performed, depending on the amount and extent of the deviations. All such analyses will be considered post-hoc.

## Appendix

### 4.7 Primary outcome analysis (objective #1)

The primary outcome is tic severity, as measured by the YGTSS-TTSS, at the primary endpoint (3FU). The primary outcome analysis (objective #1) will be based on all available data up to this time point and conducted according to the intention-to-treat (ITT) principle.

As the YGTSS-TTSS is a composite measure resulting in an integer-valued variable ranging from 0 to 50, statistical modelling will focus on the median of the outcome (i.e., the 0.5-quantile) rather than its mean. Specifically, all the randomised participants will be included to estimate a linear quantile mixed model [6-8], taking into account individual differences in pre-treatment symptomatic status and treatment response. The model will include fixed effects for time (the YGTSS-TTSS at baseline, post-treatment, and 3-month follow-up) and subject-specific effects as a random intercept factor to account for the variances between and within participants. Linear quantile mixed models use all available data, can account for correlation between repeated measurements on the same subject, can flexibly model time effects, and can handle missing data.

To enable comparisons with previous trials within the field, which traditionally have used regression models based on means rather than medians, we will also perform complementary analyses of the primary outcome measure at the primary endpoint using a linear mixed model (estimating a difference in means). Similar to the linear quantile mixed model, the linear mixed model will include fixed effects of time (the YGTSS-TTSS at baseline, post-treatment, and 3-month follow-up) and subject effects as a random intercept factor to account for the variances between and within participants. Like linear quantile mixed models, linear mixed-effects models use all available data, can account for correlation between repeated measurements on the same subject, can flexibly model time effects, and can handle missing data. Results from the linear mixed-effects model will be presented as a complementary analysis to the linear quantile mixed model.

The estimated treatment effect will be reported with the accompanying 95% confidence interval (CI) and *p*-value. The alpha level of 0.05 will be used as the threshold for statistical significance throughout all trial analyses.

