### 5.3 POWER ANALYSIS

Due to our primary and secondary outcome variables being integer-valued (ordinal) in nature, we estimated the power for the difference in *median* outcome between the two treatment groups at the primary endpoint using data from our pilot trial [15]. Specifically, we used a Wald test for the coefficient of the interaction term in a linear quantile random intercept model for the median of the outcome [29-31]. The model contained the intercept, the binary treatment indicator (BIP TIC, control condition), the numeric time variable (baseline, post-treatment, 3-month follow-up), and the treatment-by-time interaction term. We calculated the power under different samples sizes and differences in median outcome between the two treatment groups at the primary endpoint. For each combination of sample size and difference, we simulated 500 samples under a random intercept model with normal intercept and normal residual error. The regression parameters and variance components were obtained from our pilot data. The regression coefficients were 28.56 for the intercept, and – 3.11 for time, while the standard deviation of the random intercept was 2.95, and that of the residual was 2.04. These calculations showed that with 200 patients (100 in each arm) we would have 97% power to detect a statistically significant difference in medians of 3 points on the YGTSS Total Tic Severity Score at the primary endpoint. Allowing for a 10% dropout rate, this trial will aim to recruit up to 220 participants.

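### The random-intercept primary model cannot represent differences in treatment response as SAP 4.7 says; if response varies between children, model-based standard errors can be wrong and outcome-related dropout can bias the estimate

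*Combined protocol and SAP*

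**What the plan says.** SAP 4.7 says that the linear quantile mixed model will be fitted to all randomised participants, "taking into account individual differences in pre-treatment symptomatic status and treatment response". The participant-level part of that model is given as "subject-specific effects as a random intercept factor to account for the variances between and within participants". The complementary linear mixed model has the same structure: "subject effects as a random intercept factor to account for the variances between and within participants". No random slope and no other covariance structure is mentioned. Protocol 8.1 matches, and protocol section 8 gives the SAP precedence where the two differ.

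The power calculation in protocol 5.3 shares the restriction. It uses a "Wald test for the coefficient of the interaction term in a linear quantile random intercept model", and "we simulated 500 samples under a random intercept model with normal intercept and normal residual error". The pilot components are stated: "the standard deviation of the random intercept was 2.95, and that of the residual was 2.04".

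On inference, SAP 4.7 says "The alpha level of 0.05 will be used as the threshold for statistical significance throughout all trial analyses" but does not say how standard errors are obtained. SAP 4.7.1 mentions the bootstrap only as something to consider if normality plots look poor. On missing data, SAP 4.7 relies on the models to cope. SAP 4.7.2 adds a supportive analysis that adjusts for baseline predictors of missingness.

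**The concern.** A random intercept moves a child's whole profile up or down by the same amount at every visit. Nothing in it lets one child improve more than another beyond visit-to-visit noise, so the sentence and the specification do not match.

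The implied pattern (one variance, one correlation for every pair of visits) is a strong restriction here. The documents themselves expect response to vary: SAP 4.9 counts CGI-I responders, and protocol 8.5 lists candidate predictors and moderators. Protocol 5.5.2 has the same blind assessor rate a child's post-treatment and follow-up visits where possible, which would tend to make those visits more alike than baseline and follow-up.

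Two things are at stake: whether the confidence interval and p-value for the 3-month contrast are calibrated, and whether the model predicts correctly for children who leave after the post-treatment visit. No planned safeguard covers either. Normality plots do not test equal correlation across visits, and baseline predictors of missingness say nothing about dropout driven by the post-treatment score.

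**Working it through.** **Inputs from the documents.** Protocol 5.3: random-intercept SD 2.95, residual SD 2.04, 100 per arm, 3-point difference, 97% power, 10% dropout. Protocol 6.10: at least 80% with the primary outcome, so up to 20% missing is tolerated. SAP 4.7: alpha 0.05, taken as two-sided.

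**Assumed.** The documents give no slope variance and no visit-specific covariances, so ranges are shown.

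**1. The plan's own power.** For the treatment-by-time coefficient over three equally spaced visits, SE = √(2 × (2.04²/2)/100) = 0.204 for means. Multiplying by √(π/2) for medians gives 0.256. If time is coded 1, 2, 3 with no true treatment main effect, the coefficient is 3/3 = 1 and power is Φ(1/0.256 − 1.96) = 97.4%, which matches 97%. Coded 0, 1, 2, the coefficient is 3/2 = 1.5 and power exceeds 99.9%. The codes are not stated, so the match rests on that assumption.

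**2. Standard error in the linear mixed model, complete data.** Type I error is 2Φ(−1.96 × √(model variance / true variance)).

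*(a) Part of the pilot residual variance is really linear slope.* Let that share be f. The model variance is proportional to 1 and the true variance to 1 + f.

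| f | SE understated by | Type I error | Power with correct SE (time coded 1, 2, 3) |
|---|---|---|---|
| 0 | 0% | 5.0% | 97.4% |
| 0.10 | 4.7% | 6.2% | 96.2% |
| 0.25 | 10.6% | 8.0% | 93.8% |
| 0.50 | 18.4% | 11.0% | 89.1% |

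Simulation (2,000 trials) gave 4.8%, 7.9% and 11.2% at f = 0, 0.25 and 0.50. A participant-level robust standard error on the same estimate gave 4.8%, 4.8% and 5.4%. With time coded 0, 1, 2, power with the correct SE stays at or above 98.6% even at f = 1.

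*(b) A lasting individual shift, SD τ, at both post-baseline visits, added to residual SD 2.04.* For the baseline-to-follow-up change, true variance is 2 × 2.04² + τ² and model variance is 2 × (2.04² + τ²/3).
- τ = 1: 9.32 against 8.99, type I error 5.4%.
- τ = 3: 17.32 against 14.32, type I error 7.5%.

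*(c) A transient shift at post-treatment only.* True variance is 2 × 2.04² = 8.32; model variance is as in (b).
- τ = 1: 8.32 against 8.99, type I error 4.2%.
- τ = 3: 8.32 against 14.32, type I error 1.0%.

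*(d) Assumed full covariances.* Model variance is 2 × (mean variance − mean covariance). True variance is that of the change from baseline to follow-up. Correlations are in the order baseline–post, baseline–follow-up, post–follow-up.

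| Visit SDs | Correlations | Model variance | True variance | Type I error |
|---|---|---|---|---|
| 3.59, 4.5, 5 | 0.60, 0.50, 0.75 | 15.06 | 19.94 | 8.8% |
| 6, 7, 7 | 0.70, 0.60, 0.80 | 26.80 | 34.60 | 8.5% |
| 6, 6, 6 | 0.60, 0.50, 0.80 | 26.40 | 36.00 | 9.3% |

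Simulation with an unstructured covariance gave 5.0 to 5.1%.

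**3. Bias at 3 months, linear mixed model.** Large-sample simulation, true difference −3. Dropout after the post-treatment visit depends on the observed change. In the opposite-mechanism rows, control non-responders and active-arm responders leave. Each range runs from numeric to categorical time.

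| f | Missing | Same mechanism | Opposite mechanisms |
|---|---|---|---|
| 0 | 10% or 20% | within 0.02 | within 0.02 |
| 0.25 | 10% | 0.01 to 0.02 | 0.08 to 0.10 |
| 0.25 | 20% | 0.02 | 0.14 to 0.18 |
| 0.50 | 10% | 0.04 to 0.05 | 0.20 to 0.24 |
| 0.50 | 20% | 0.06 to 0.09 | 0.34 to 0.43 |

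Here the bias is towards no effect. The random intercept uses a departing child's post-treatment score too little. Control non-responders are therefore predicted too low and active responders too high. Reversing who leaves reverses the sign. A random-slope model brought the bias to within about 0.03.

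For the quantile model at f = 0.5 with opposite mechanisms, two large fits per setting averaged about 0.2 at 10% missing and 0.4 at 20%. Those fits were noisy.

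**The case against.** The mismatch in wording is hard to contest; its consequences are not automatic. A reader might infer that the primary test rejects too often and that its estimate is biased. The documents do not support either as a plain statement, for four reasons.

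- **The primary test was not evaluated for type I error.** All type I error figures are for the complementary linear mixed model with a model-based standard error. The SAP leaves the quantile model's method open, and participant-level inference would repair calibration without changing the model.
- **The direction is not fixed.** A transient post-treatment shift makes the test conservative. The documents point more towards lasting response and a shared assessor than towards a transient shift, but they settle nothing.
- **The larger covariances go beyond the stated variability.** Protocol 5.3 implies an SD of change of 2.04 × √2 = 2.88, whereas the matrices in (d) imply 4.5, 5.9 and 6.0. It is also tempting to argue that the entry threshold compresses baseline spread. On the protocol's figures the cut-off of 15 lies (28.56 − 15)/3.59 = 3.8 SD below the intercept, so that adds little.
- **The larger dropout bias needs an unfavourable combination.** Planned dropout is 10%, the pilot lost no data (protocol 3.2), and children who stop treatment are still invited to assessments (protocol 6.8). Opposite mechanisms by arm near 20% missing is close to a worst case.

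All four stand. They make the consequences conditional. They do not remove the mismatch or supply the missing safeguard.

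**Conclusion.** The specification does not do what SAP 4.7 says it does, and nothing prespecified covers the gap. The consequences depend on response varying between children.

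- **Calibration** (linear mixed model, model-based standard error, 100 per arm): about 5 to 7.5% for a lasting shift around the protocol 5.3 components, about 8 to 11% with stronger heterogeneity, below 5% for a transient shift.
- **Bias** on a 3-point effect: at most about 0.1 points with the same mechanism in both arms; with opposite mechanisms, up to about 0.25 at 10% missing and about 0.4 at 20%, with a sign that depends on who leaves. There is none if compound symmetry holds.

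This should be fixed before unblinding because it concerns the confirmatory analysis, but it is not shown to invalidate it. The secondary and stage 2 models inherit the structure; no calculation was made for them.

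**What to change.** In SAP 4.7, before unblinding:

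1. Fit the complementary linear mixed model with categorical visit, visit-by-arm and an unstructured 3 × 3 covariance.
2. Take the confidence interval and p-value of the quantile mixed model from a bootstrap that resamples whole participants within arm, as the rule and not as a contingency. Do the same for the linear mixed model, or use a participant-level robust standard error there.
3. Delete the reference to treatment response from the description of the random-intercept model. Prespecify, as a sensitivity analysis subject to convergence, a quantile mixed model with an added random post-baseline (time) effect. With three visits per child its estimability is untested, so it should not replace the primary model.

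Item 2 protects the standard error but does not remove dropout bias. Item 1 addresses that bias in the linear mixed model, and item 3 shows how sensitive the quantile estimate is. None of them cures dropout that depends on unobserved scores.

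The cost is SAP wording, a few lines of code, computing time, four more covariance parameters (six instead of two) and possibly slightly wider intervals. SAP 4.2 already requires the primary analysis code before unblinding, and under SAP 1.1 adaptations to the plan must be labelled post-hoc.

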#### 4.7.1 Model checking

The statistical model for the primary outcome analysis includes an assumption that the subject-specific random intercepts are normally distributed. This assumption will be checked through the construction of appropriate histograms and normal quantile plots. If these plots suggest that residuals are not normally distributed, then appropriate transformations of the primary outcome or application of the bootstrap method will be considered.

#### 4.7.2 Missing data

Potential selection bias caused by missing data will be investigated by comparing the baseline characteristics of participants with and without missing values on the YGTSS-TTSS using logistic regression. Depending on the amount of missing values, predictors of missingness will be identified. We will then perform a sensitivity analysis by including any predictors of missingness as explanatory variables in the primary outcome model. Analyses investigating the impact of missing data will be considered supportive.

## **Appendix**

### **4.8 Analyses of secondary outcomes**

Secondary outcome measures (details shown in the full study protocol) will be analysed using similar statistical methods as the primary outcome, that is, with linear quantile mixed models, and complemented with linear mixed models to facilitate comparison with previous trials. Dichotomous variables will be analysed using logistic regression. The results will be presented as estimates or odds ratios, as appropriate, for the regression coefficients, with their respective 95% confidence intervals and *p*-values.

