#### ***Clinical Global Impression Scale – Improvement (CGI-I)***

The CGI-I [40] provides a clinician-rated opinion of global improvement. The measure consists of one single item, asking about the level of improvement compared to admission, which is rated according to the following: 1=very much improved; 2=much improved; 3=minimally improved; 4=no change from baseline (the initiation of treatment); 5=minimally worse; 6=much worse; 7=very much worse”. By convention, scores of “very much improved” (1) or “much improved” (2) define treatment response in clinical trials of TD [17]. The questionnaire has established validity and reliability [41]. All assessors will practice rating CGI-I together and inter-rater reliability will be calculated. The CGI-I can be completed in less than a minute by an experienced rater.

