## 8.5 PREDICTOR AND MODERATOR ANALYSIS

Post-hoc analyses may be conducted investigating predictors and moderators of treatment response. More specifically, the following variables can be hypothesised to potentially predict or moderate treatment outcomes: a) tic severity (measured by the YGTSS TTSS [28]), b) degree of premonitory urge (measured by the PUTS [38]), c) OCD symptoms (measured by the OCI-CV [49]), d) ADHD symptoms (measured by the SNAP-IV [35]), e) autism symptoms (measured by the AQ-10 [34]), and f) medication status [63]. Additionally, we predict that adherence during treatment (measured by the iiPAS, therapist time, number of logins and sent messages) and also motivation to complete the treatment (measured using the Treatment credibility scale, item 3, at week 3) will significantly predict or moderate treatment outcomes.

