### **4.9 Treatment response**

Treatment response will be operationalised as scores of “very much improved” (1) or “much improved” (2) on the Clinical Global Impression – Improvement scale (CGI-I) administered at 3FU [9]. We will also report numbers needed to treat, with 95% confidence intervals, based on the proportions of responders in each group at 3FU.

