## Appendix

The Trimbos/iMTA Questionnaire for Costs associated with Psychiatric Illness (TiC-P [12]) will be administered (in an adapted version for young people and parents) at each assessment point (except 3 and 5 weeks into the treatment) to collect information on frequencies of resource use for the children and absenteeism from work for the parents. Resource use costs will be estimated by multiplying frequencies by national Swedish tariffs and market prices. Total costs for each group will be aggregated over the trial period.

For each of the three perspectives above, we will conduct two types of analyses:

1. A cost-effectiveness analysis, using responder rate as the outcome [13].
2. A cost-utility analysis using Quality Adjusted Life Years (QALYs) as the outcome [13].

Health gains in terms of QALYs will be estimated by mapping KIDSCREEN-10 scores [14] onto Child Health Utility 9 Dimensions (CHU9D) utility weights [15]. Total QALY gains over the trial period will be estimated by using the area under the curve method [16]. Differences in QALYs and costs between both trial arms will be investigated using generalised linear models with suitable distributions [17].

To ascertain whether BIP TIC is cost-effective, relative to the comparator, incremental cost-effectiveness ratios expressed as cost per additional responder and cost per additional QALY will be presented. The uncertainty around the cost and effect estimates will be presented using a cost-effectiveness acceptability curve [13].

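### SAP 4.8 and 4.9 name no baseline covariates for the CGI-I response model; prespecifying baseline tic severity and tic medication would be a cheap, modest efficiency gain on a secondary outcome

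*Combined protocol and SAP*

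**What the plan says.** SAP 4.9 defines the responder outcome: "Treatment response will be operationalised as scores of" 1 or 2 on the CGI-I at the 3-month follow-up. SAP 4.8 gives the method for binary outcomes: "Dichotomous variables will be analysed using logistic regression". On reporting it says: "The results will be presented as estimates or odds ratios, as appropriate, for the regression coefficients, with their respective 95% confidence intervals", plus p-values. SAP 4.7 sets the threshold: "The alpha level of 0.05 will be used as the threshold for statistical significance throughout all trial analyses".

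Response has two further uses. SAP 4.9 adds: "We will also report numbers needed to treat, with 95% confidence intervals, based on the proportions of responders in each group at 3FU". SAP 5.2 lists: "A cost-effectiveness analysis, using responder rate as the outcome".

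Neither 4.8 nor 4.9 lists covariates. The SAP mentions extra explanatory variables only in 4.7.2, for a supportive missing-data analysis of the primary outcome.

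Baseline YGTSS-TTSS is in protocol Table 1, and current tic medication is among the clinician-entered baseline data in protocol 5.5.1. Protocol 6.1.2 requires all baseline measures to be answered before randomisation. Protocol 6.2 describes 1:1 allocation in randomly varying blocks, with no stratification. Protocol 8.5, on optional post-hoc work, says "the following variables can be hypothesised to potentially predict or moderate treatment outcomes: a) tic severity" and lists medication status as item f.

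**The concern.** YGTSS-TTSS is measured at baseline and carries that value into its mixed model. CGI-I has no baseline assessment, so response enters as a single binary value per child. If arm is the only term, any prognostic information in baseline severity and medication goes unused, although both should be essentially complete for everyone randomised. Nor does the design as described balance the arms on them.

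The stake is the power of the responder test and the width of any absolute effect derived from it. There is also a specification issue. SAP 1.1 says that the analyses are fixed in advance so that unblinded data cannot influence them, and a model with no stated terms leaves the choice of covariates open.

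**Working it through.** **Plan's own figure.** The documents give no power for CGI-I response. Their one power figure, 97% in protocol 5.3, is for a 3-point difference in median TTSS. A rough check with the protocol's standard deviations gives a total SD of √(2.95² + 2.04²) = 3.587. The standard error of a difference in medians is then √(π/2) × 3.587 × √(2/100) = 0.636, and Φ(3/0.636 − 1.96) is about 99.7%. That does not reproduce 97%, but nothing below depends on it.

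**Inputs.**
- From the documents: 100 evaluable children per arm (protocol 5.3), 1:1 allocation (protocol 6.2), alpha 0.05 (SAP 4.7).
- Assumed: a two-sided test (sidedness is not stated), the response rates, and the share R² of latent response variance that the baseline covariates explain. The documents give none of these, so ranges are shown.

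**Arm-only model, 20% v 35%.**
- Log odds ratio = ln[(0.35/0.65)/(0.20/0.80)] = 0.767.
- SE = √[1/(100 × 0.35 × 0.65) + 1/(100 × 0.20 × 0.80)] = 0.326.
- z = 2.352; power = Φ(2.352 − 1.96) = 65.2%.

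**Adjusted model.** Let logit P(response) = α + β·arm + γX, with X a standard-normal baseline score and γ² = [R²/(1 − R²)] × π²/3. Solve α and β so that the marginal rates stay at 20% and 35%, and take the SE of β from the inverse Fisher information. At R² = 0.10:
- γ² = 0.1111 × 3.290 = 0.366, an odds ratio of 1.83 per SD of X.
- β = 0.820, SE = 0.338, z = 2.424; power = Φ(2.424 − 1.96) = 67.9%.

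The SE of the log odds ratio rises from 0.326 to 0.338 and the odds ratio moves from 2.15 to 2.27. Power rises because β grows faster than its SE.

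**Power across assumptions (%, by the same formulas).**

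| Control / BIP TIC | Arm only | R² 5% | R² 10% | R² 20% | R² 30% |
|---|---|---|---|---|---|
| 15 / 30 | 70.5 | 71.7 | 72.8 | 75.3 | 77.9 |
| 20 / 35 | 65.2 | 66.5 | 67.9 | 70.7 | 73.6 |
| 20 / 40 | 86.0 | 86.9 | 87.9 | 89.7 | 91.5 |
| 30 / 45 | 58.7 | 60.2 | 61.7 | 64.8 | 68.1 |
| 30 / 50 | 81.7 | 82.9 | 84.1 | 86.4 | 88.7 |
| 20 / 50 | 99.1 | 99.2 | 99.3 | 99.5 | 99.7 |

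Outside the last row the gain is 0.9 to 1.5 points at R² 5% and 1.9 to 3.0 points at R² 10%. At R² = 0 it is nil.

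**Simulation checks.** With 2,000 trials per cell, power rose from 83.2% to 86.6% for 30/50% and from 87.6% to 89.8% for 20/40%, both at R² 10%. With 10,000 trials per cell, 20/35% went from about 66% to 67% and 69% at R² 5% and 10%, and type I error stayed near 5%.

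**Standardised risk difference, 20% v 35%.**
- Crude variance = (0.35 × 0.65 + 0.20 × 0.80)/100 = 0.003875; SE 0.0622.
- Adjusted variance = {2·E[p₁(1 − p₁)] + 2·E[p₀(1 − p₀)] + Var(p₁ − p₀)}/200, where p₁ and p₀ are the response probabilities given X under each arm. At R² 10% the SE is 0.0602.
- Ratio of variances = (0.0622/0.0602)² ≈ 1.07, as if about 14 children were added to 200.

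**NNT.** The point value is 1/0.15 = 6.7 either way. From the crude SE, the risk difference is 0.15 ± 0.122, so the NNT runs from 3.7 to 35.6. From the adjusted SE it is 0.15 ± 0.118, so the NNT runs from 3.7 to 31.3.

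**The case against.** The strongest reply is that nothing here is an error. An arm-only comparison in a 1:1 trial with no described stratification is valid, the trial was powered on TTSS, and CGI-I response is secondary. That stands.

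The gain is also conditional. CGI-I already rates change, "asking about the level of improvement compared to admission", so starting severity may predict it only weakly. The entry criteria cut off low severity scores and require stable tic medication. Nothing in the documents supports R² of 20 to 30%. This stands too, and is why the 5 to 10% range carries the conclusion.

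A reader might infer four stronger things that the documents do not support:
- *That the SAP chose an unadjusted model.* It never says so. Arm-only is the natural reading, but the text is silent.
- *That the sponsor expects these variables to predict outcome.* Protocol 8.5 only hypothesises that they may predict or moderate, and a moderator need not be prognostic. Its firm prediction concerns adherence and motivation, which are measured after randomisation and so cannot serve as baseline covariates.
- *That adjustment makes the reported odds ratio more precise.* The SE of its logarithm rises.
- *That the NNT and cost per responder suffer through the logistic model.* The NNT uses the proportions and the economic analysis uses the responder rate. Covariates in the 4.8 model change neither unless the quantity is derived from the standardised estimate.

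Protocol 8.5 also lists premonitory urge and OCD, ADHD and autism symptoms, so the choice of two covariates is a judgement. The case for them is that both are recorded before randomisation and bear directly on tics. A different short list fixed in advance would also close the specification gap.

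**Conclusion.** The point holds as a minor efficiency and specification improvement on a secondary outcome. It rests on assumed response rates, an assumed R², a single normally distributed baseline score standing in for the two covariates, and 100 evaluable children per arm. The gain is about 1 to 3 power points at R² of 5 to 10%, but almost nothing at 20/50%, where power is already 99%. Across the six assumed pairs, R² of 20% gives 0.4 to 6.1 points. The documents cannot show where in this range the trial lies, so a reader should not infer that a known amount of power is being lost, or that the planned comparison is biased.

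**What to change.** In SAP 4.8/4.9, before unblinding:
- State that the logistic model for CGI-I response at the 3-month follow-up contains arm, baseline YGTSS-TTSS as a continuous variable, and tic medication at baseline (yes/no).
- Report the conditional odds ratio together with the standardised risk difference, each with a 95% CI.
- Derive the NNT and its interval from that risk difference.
- Show the crude proportions and the unadjusted result as a check.

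The cost is a few sentences and two variables that are already collected. SAP 4.2 finalises the SAP and prepares the primary-analysis code before unblinding, so the change fits the existing timetable. The downside is small: the adjusted odds ratio is conditional, lies further from 1 and has a larger SE on the log scale, which is why the risk difference should stand beside it. If the covariates prove not to be prognostic, two extra terms in a model of about 200 children cost almost nothing.
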